### Sample size calculation

Using pairwise comparison simulations, we set analysis parameters to achieve a false-positive rate of < 5% and a power of ~ 80% for detecting an effect size of d = 0.6. The choice of effect size was revised after the trial commenced but prior to the start of sequential analysis, based on a recent meta-analysis of iTBS [48]. Initially, we selected an effect-size of 0.8 due to practical considerations, including the absence of specific evidence for iTBS in younger populations and constraints on trial funding. For N_min_ = 26; N_max_ = 45; BF_fail_ = 1/5; and BF_success_ = 5, simulations with up to 15% missing data suggest that these parameters provide a < 5% false-positive rate and 71.35% power to reach the BF_fail_ threshold before recruitment of N_max_ when d = 0; and 81% power to hit BF_success_ before N_max_ for an effect size of d = 0.6(see Table 2). For practical purposes, N_max_ will be operationalized on the basis of the total sample size, that is, when the total number of participants randomized is 2 × N_max_ (i.e., *N* = 90), regardless of the distribution across arms. Simulation scripts and results of the initial and revised sample size calculations are available at 10.17605/OSF.IO/B397U.

**Table 2 Tab2:** Pairwise comparison simulations using cLDA

	Probability of hitting BF threshold at each participant number (per group)									
	Hit BFfail					Hit BFsuccess				
d	26	30	35	40	45	26	30	35	40	45
− 0.2	73.85	82.45	87.20	90.90	93.40	0.20	0.45	0.45	0.70	0.70
0	46.20	55.60	62.05	67.20	71.35	**1.30**	**1.95**	**2.45**	**2.75**	**3.00**
0.2	18.85	25.15	30.15	33.40	35.40	6.20	9.95	13.10	15.75	17.95
0.3	11.45	15.90	18.65	20.40	22.10	12.85	18.05	22.25	26.50	29.55
0.4	5.45	7.25	8.55	9.70	10.15	21.85	31.10	37.55	42.75	47.45
0.51	2.00	2.95	3.40	3.85	4.00	34.65	45.60	54.10	60.25	66.55
0.6	1.25	1.55	1.85	1.95	2.00	**48.95**	**60.25**	**69.45**	**76.25**	**81.15**
0.71	0.30	0.50	0.55	0.55	0.55	63.10	74.65	82.55	87.15	91.10
0.8	0.05	0.20	0.20	0.20	0.20	74.15	83.35	89.80	92.65	95.35

Bold values indicate false-positive rate and power estimates for an effect size of 0.6

Simulations for the following parameters: N_min_ = 26, N_max_ = 45, BF_fail_ = 1/5, BF_success_ = 5; 15% missing data. Simulations were conducted in RStudio running R version 4.2.2, using 2000 simulations. Estimated effect sizes (d) are a form of Cohen’s d estimated from a t-test on the change scores between groups, with positive d values indicating superiority of the treatment condition to the sham condition. Although d values at intervals of 0.1 were simulated (e.g. 0.2, 0.3, 0.4), the table presents the mean observed effect size across the simulations, which often deviate slightly from these values.

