**Fig. 3 Fig3:**
[figure not shown]
Sequential Bayesian analysis design

Analyses will follow an intention-to-treat approach, including all participants randomized to a condition, irrespective of intervention completion or outcome data availability. For sensitivity analyses, participants will be classified as per protocol if they complete the 6-week treatment period and receive at least 20 treatment sessions within six weeks. Sequential analyses will commence once each arm meets the predefined minimum sample size N_min_. Analyses will be updated with each participant’s trial completion. Following Blackwell et al. (2022), missing data will be handled using constrained longitudinal data analysis (cLDA) via the R package nlme [44]. Bayes factors will be estimated with the R package BayesFactor [45] using the t-statistic for the Time x Group interaction and directional default Cauchy prior (rscale parameter = √2/2). Effect sizes (adjusted Cohen's d) and estimated means for the primary outcome, along with their 95% confidence intervals (CIs), will be derived from the cLDA model using the R packages effectsize [46] and emmeans [47]. Analyses will be performed by a statistician ([name]) aware of participant allocation (given the directional nature of the analyses), sharing results with the research team only if a BF boundary is met or after N_max_ is reached.

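### With participants per arm as n, the stated Bayes factor gives about 58%, not 71.35%, for reaching BF_fail under d = 0; the n and rscale behind Table 2 need to be stated

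*Protocol article*

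**What the plan says.** Statistical methods and analysis fixes most of the Bayes factor. It is computed with the R package BayesFactor, "using the t-statistic for the Time x Group interaction" from the cLDA model, under a "directional default Cauchy prior (rscale parameter = √2/2". On timing, "Analyses will be updated with each participant" who completes, once each arm has N_min. The trial halts when either threshold is crossed, so BF_fail is a binding stopping rule.

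The footnote to Table 2 gives the simulation settings: "Simulations for the following parameters: N_min_ = 26, N_max_ = 45, BF_fail_ = 1/5, BF_success_ = 5; 15% missing data", with 2000 runs. The table's columns are headed "Probability of hitting BF threshold at each participant number (per group"). Its d = 0 row for BF_fail reads 46.20, 55.60, 62.05, 67.20 and 71.35 at 26, 30, 35, 40 and 45 per group, and the text carries the last value forward as "71.35% power to reach the BF_fail_ threshold before recruitment of N_max_ when d = 0".

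The article does not state the group sizes n1 and n2 that accompany the t-statistic. A Bayes factor computed from a t-statistic depends on them directly.

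**The concern.** At 26 per group only one look has been taken. Under d = 0 the chance of crossing BF_fail there is a single t-tail probability, which can be checked without simulating the trial. With 26 participants per arm and the stated prior it is about 31%, far from the printed 46.20%.

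Two things could be at stake, depending on what the trial's analysis does:

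- If the analysis uses participants as n, the article overstates how often an ineffective treatment is identified within 90 patients.
- If the analysis uses whatever produced Table 2, the trial may stop for lack of superiority on weaker evidence than the 1/5 it will report.

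**Working it through.** **Inputs from the article.** rscale r = √2/2 = 0.7071; directional prior; BF_fail = 1/5; BF_success = 5; N_min = 26 and N_max = 45 per arm; 15% missing; 2000 simulations.

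**Assumed.** Pre-post correlation 0.5, which is not stated; 0.3 to 0.7 was tried and hardly moves the d = 0 row. Missingness completely at random in the week-6 value.

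**Formula.** For n per arm and df = 2n − 2,

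BF₊₀(t) = ∫₀^∞ f_nct(t; df, δ√(n/2)) · 2 · Cauchy(δ; 0, r) dδ ÷ f_t(t; df).

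Solve BF₊₀(t) = 1/5 for t. The first-look BF_fail probability at d = 0 is P(T_df < t).

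**First look, d = 0 (printed: 46.20%).**

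| n per arm in the Bayes factor | rscale | t where BF = 1/5 | P(BF_fail) |
|---|---|---|---|
| 26 participants | 0.707 | −0.51 | 30.6% |
| 22.1 (26 × 0.85, with week-6 data) | 0.707 | −0.64 | 26.4% |
| 48.1 rows (26 baseline + 22.1 week 6) | 0.707 | −0.095 | 46.2% |
| 26 participants | 0.95 | −0.11 | 45.6% |
| 26 participants | 1 | −0.05 | 48.1% |
| 22.1 with week-6 data | 1 | −0.15 | 44.2% |

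The Monte Carlo standard error of the printed value is √(0.462 × 0.538 / 2000) = 1.1 points. The gap of 46.2 − 30.6 = 15.6 points is about 14 standard errors.

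**Sequential simulation, d = 0.** 20,000 runs, two-time-point cLDA (ANCOVA-type) test, 15% missing, cumulative % reaching BF_fail:

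| Per group | 26 | 30 | 35 | 40 | 45 |
|---|---|---|---|---|---|
| Table 2 | 46.20 | 55.60 | 62.05 | 67.20 | 71.35 |
| r = √2/2, participants | 30.8 | 40.3 | 47.9 | 53.5 | 58.1 |
| r = √2/2, observation rows | 46.0 | 56.1 | 62.9 | 67.8 | 71.6 |
| r = 1, participants with data | 44.6 | 54.7 | 61.8 | 67.1 | 71.2 |

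With participants as n, the value at 45 per arm is 57.8% with a change-score test, 58.6% with no missing data and 59.7% with a look after every single participant. It is 53% to 54% if n counts only participants with week-6 data. None of these approaches 71.35%.

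**Other effect sizes, BF_fail by 45 per arm** (6,000 runs each, r = √2/2):

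| d | Table 2 | participants | rows |
|---|---|---|---|
| −0.2 | 93.40 | 88.5 | 93.8 |
| 0.2 | 35.40 | 23.0 | 35.8 |
| 0.3 | 22.10 | 12.2 | 21.9 |
| 0.4 | 10.15 | 5.0 | 10.8 |
| 0.51 | 4.00 | 1.7 | 4.3 |
| 0.6 | 2.00 | 0.6 | 2.0 |
| 0.8 | 0.20 | 0.0 | 0.2 |

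**BF_success half.** At d = 0, participants as n gives about 3.3% (3.00% printed). At d = 0.6 it gives 82.5%, and rows give 79.8% (81.15% printed). This half fits the printed values on either reading, so the simulation model is adequate and the discrepancy is confined to BF_fail.

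**Inconclusive null trials at N_max.** Table 2: 100 − 71.35 − 3.00 = 25.65%. Participants as n: 100 − 58.1 − 3.3 = 38.6%.

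**What the row-count cut means.** Putting its first-look cut, t = −0.095, into the formula with n = 26 and r = √2/2 gives BF₊₀ = 0.26, about 1/3.8.

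**The case against.** The strongest reply is that the article never states n1 and n2. Keep every parameter it does state, let n be the number of observation rows, and the BF_fail column comes back within about 2 points. A reader might therefore infer from the first-look gap that the printed figures cannot come from the stated Bayes factor, or that the stated rscale is wrong. The article supports neither inference. Participants as n is the natural reading, because the columns are headed by participants per group and a two-group t-test Bayes factor takes independent subjects, but it remains a reading.

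Nor is the cause identified. An rscale of 1 with participants who have data ends at 71.2%, almost as close as row counting. The scripts in the cited repository would settle it, but they were not available for this check. Any harm argued from row counting is therefore conditional.

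A reader might also take the whole BF_fail half to be wrong. At d = 0.71 and above both readings are near zero and cannot be told apart.

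Finally, the two design targets, a false-positive rate below 5% and about 80% power at d = 0.6, hold on either reading, and the Discussion already concedes that the trial may reach its maximum without conclusive evidence. That limits the consequence. It does not explain the 71.35%, which is printed as an operating characteristic of a binding stopping rule.

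**Conclusion.** The point holds in this form: with rscale √2/2, BF_fail = 1/5, 15% missing data and participants per arm as n, the BF_fail figures for d from −0.2 to 0.6 do not reproduce. At d = 0 the article overstates the chance of reaching BF_fail by about 15 points at the first look and about 13 points by 45 per arm, against a Monte Carlo error of about 1 point.

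What follows depends on the code. If the sequential analysis uses participants as n, about 58% applies. If it uses the call that produced Table 2, 71.35% correctly describes how often the trial stops, and the defect is an undocumented n or prior. Should that call count rows, the first-look futility cut sits at a participant-level Bayes factor of about 0.26, and wrongful futility is about double that of a true 1/5 boundary (d = 0.3: about 22% against 12%; d = 0.4: about 10% against 5%). The figures for d other than 0 rest on the assumed correlation of 0.5.

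**What to change.** Before the first sequential look, and in the ethics amendment on sample size that the article says is being prepared:

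1. State the n1, n2 and rscale passed to BayesFactor, in the simulation and in the sequential analysis.
2. Use participants per arm, not repeated observation rows, as n with rscale √2/2, and say whether participants without week-6 data count. Make both scripts use the identical call.
3. Re-run the simulation and restate Table 2 and the 71.35% (about 58%, or about 54% if only participants with week-6 data count).
4. If the sponsor prefers to keep the boundary that was simulated, state the prior, n or BF_fail value really used, and report the evidence level and wrongful-futility rates that go with it.

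The cost is one script re-run, one table and one or two sentences; no extra patients. The futility figure becomes less favourable. Timing matters because a boundary changed after the first look would be open to the charge of being data-driven. With one participant enrolled at submission, the change could be made well before then.

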### Patient and public involvement

A patient and public representative (PB) has reviewed the patient information and consent documents, contributed to this manuscript, and will participate in recruitment, safety monitoring, interpretation of results, dissemination of results, and writing of the final report.

### Ethical approval and dissemination

The Ethics Committee of the Medical Faculty of the Ludwig Maximilian University Munich approved the first version of the study protocol (version 1.0) on 09.06.2023 and the latest version (version 1.2) prior to the start of recruitment on 22.03.2024. An amendment of the protocol containing revised sample size calculations is currently prepared for submission to the Ethics Committee. The trial has been registered at the German Clinical Trials Register (https://www.drks.de/drks_web/; DRKS00033313). It will be conducted in accordance with the Declaration of Helsinki and GCP-ICH guidelines. The study's results will be published regardless of the outcome.

### Trial status

Recruitment of participants started on 01.04.2024. As of the submission date of this manuscript, one participant has been enrolled in the trial.

## Discussion

Depressive disorders frequently emerge during the transition phase from adolescence to adulthood, carrying significant adverse health consequences. As shown by prior RCTs in MDD, iTBS targeting the DLPFC is a safe and effective non-invasive brain stimulation (NIBS) intervention that could broaden the range of available treatment options in this transition phase. The EARLY-BURST pilot trial investigates the efficacy and safety of iTBS vs sham iTBS in reducing depressive symptoms in adolescents and young adults. While the use of concurrent pharmacotherapy will be limited to on-demand medication, psychotherapy and other psychosocial interventions will be allowed throughout the trial. Thus, iTBS will be evaluated as an additional treatment in a standard-of-care setting.

Acknowledging the heterogenous and evolving clinical manifestation in young patients [49] and based on meta-analytic evidence for the efficacy of left DLPFC rTMS in depressive syndromes across a transdiagnostic spectrum [7], our study includes adolescents and young adults with MDD, PDD, and BD and allows for pertinent comorbidities, except where such conditions likely disrupt trial procedures (e.g., mania, severe borderline psychopathology) or where alternative treatments are required (e.g., obsessive–compulsive disorder). In contrast to RCTs in adults that advocate for accelerated or high-intensity iTBS protocols to mitigate depressive symptoms [50], we opted for a standard iTBS variant only minimally modified from the original Huang et al. [27] protocol and will apply this protocol for 30 sessions within six weeks. This choice is based on the efficacy of a longer iTBS treatment duration in adults demonstrated in multicenter trials [5], recent trials indicating limited efficacy of shorter treatment protocols (i.e. only 10 sessions within two weeks) in younger patients [13], and target involvement by this protocol as shown in a recent interleaved TMS-fMRI study [28]. Moving away from the usual heuristic selection of treatment parameters in treatment development research, our trial employs a sequential Bayesian design that can be later expanded into an adaptive multiarm leapfrog trial allowing for ongoing refinements of the treatment protocol. Specifically, if the active iTBS group reaches the superiority threshold (BF_success_), it replaces the sham group as the comparison arm. New treatment arms with novel rTMS targets and protocols could then be added and tested within a running platform trial. These arms can be informed by emerging clinical evidence (e.g., introducing bilateral or accelerated stimulation based on results from ongoing trials [51, 52]), participant feedback (e.g. reducing the number of stimulation sessions to minimize attrition), or secondary analyses of current trial data (e.g., shortening the treatment duration if improvement plateaus are observed in the active iTBS group). Using a leapfrog rolling design, each active comparison arm can subsequently be superseded by new arms that demonstrate superiority, while underperforming arms exit the trial. This frees up resources to either introduce alternative treatment settings or concentrate efforts on existing arms. This iterative process continues until researchers determine that an optimized intervention is ready for large-scale confirmatory trials, or it can be perpetually embedded in routine practice as a platform for continually testing new ideas. Compared to traditional treatment development, which typically involves series of small, sham-controlled studies, this approach reduces required sample sizes, minimizes exposure to sham treatments or ineffective versions of the intervention, and rapidly incorporates new knowledge within an existing trial infrastructure, without the need to setup separate parallel trials. Thus, this pilot trial represents the initial phase in a translational framework aimed at systematically optimizing promising treatment modalities prior to launching more resource-intensive confirmatory multicenter trials.

Our trial has several limitations. First, due to practical and financial constraints, we have set a maximum number of participants, at which point the trial will conclude, potentially without delivering conclusive evidence regarding the efficacy of the active treatment. Should preliminary results show promise, discussions on extending the trial with funders may be feasible [53]. Secondly, the scope of this trial does not yet extend to conducting a full sequential adaptive trial capable of comparing various TBS parameters due to current constraints by limited funding. Thirdly, given the absence of studies specifying an age range where DLPFC connectivity is more susceptible to rTMS, we opted to include patients aged 16–26 years. This decision was based on the availability of a structured diagnostic interview validated for depressive disorders within this age group (DIPS). Fourthly, due to the lack of validated measurement instruments for self-reported anhedonia, depression, and anxiety that cover both adolescent and adult age groups, we chose to include the DASS-21 and DARS, despite their validation being limited to adult populations. Lastly, given its limited scale, this pilot trial will likely not be suited to detect moderating or mediating variables with small effect sizes in post-hoc analyses.

In conclusion, the EARLY-BURST trial aims to provide initial evidence on the efficacy and safety of iTBS for reducing depressive symptoms in adolescents and young adults with depressive disorders. Should the results prove positive, this trial could serve as the basis for subsequent iterative optimizations of the tTBS protocol and be extended to an adaptive platform trial. However, refined protocols would still necessitate validation by confirmatory multicenter RCTs prior to clinical application.
